**Long-term outcomes of NHS Health Checks in England.**

1. **Lay Summary (Max. 200 words)**

The NHS Health Check (NHSHC) is a primary prevention programme aimed at reducing important causes of mortality in England. The programme targets individuals aged 40 to 74 years and estimates their risk of heart disease, stroke, type 2 diabetes, chronic kidney diseases and some forms of dementia. After identifying individuals at elevated risk, a personalised risk management intervention is provided. As part on ongoing evaluation of the programme’s outcomes, we aim to use CPRD data to evaluate the long-term impact of the NHSHC programme, since its introduction in 2009. In this study, we aim to evaluate changes in risk factors, risk factor management, occurrence of strokes and heart attacks and mortality outcomes. This will be done by comparing these measures between a sample who participated in the health check programme and a matched control who did not initially receive a health check. The results will provide a non-randomised assessment of the programme’s effectiveness through continuing monitoring and evaluation.

1. **Technical Summary (Max. 200 words)**

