**Objectives:**

1. To test the hypotheses that greater changes in CVD risk factors, CVD risk score and CVD risk management follow the NHS Health Check than are observed in control participants;
2. To test the hypothesis that all-cause mortality and the incidence of clinical events (new diagnoses of ischaemic heart disease, stroke, diabetes mellitus and chronic kidney disease) may be lower in participants who received NHS Health Checks than control participants;
3. To test the hypothesis that inequalities in the outcomes of Health Checks across deprivation category may be lower in NHS Health Check participants than in control participants.
4. **Background**

Cardiovascular disease is the leading cause of death worldwide and in the United Kingdom (1). Almost 155,000 deaths annually are caused by CVD in UK, accounting for more than a quarter of all deaths (2). Diabetes also is increasing in frequency, with four million people in UK living with diabetes, which is associated with serious complications leading to disability and premature mortality (3).The NHS Health Check (NHSHC) is a primary prevention programme that was introduced in England. The programme targets individuals aged 40 to 74 years, who have not yet developed CVD and are not treated for elevated risk, and estimates their risk of heart disease, stroke, type 2 diabetes, chronic kidney diseases and some forms of dementia (4). After identifying individuals at elevated risk, a personalised risk management intervention is provided. This programme provides an opportunity in terms of addressing multiple risk factors which, if successful, might reduce the risk of several diseases. Results from the Department of Health economic model suggested that the NHS Health Check could save 650 lives, and 1600 heart attacks and 4000 cases of diabetes could be prevented a year (5).

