**Sample power calculation:**

Assuming that the background incidence of CHD is about 3 per 1,000 per year and the type 1 error rate is set at 0.05, if there are 75,000 health check participants and 182,000 control participants, there will be more than 90% power to detect a risk ratio of 0.85, for reduction of CHD incidence, over three years of follow-up.

1. **Data Linkage Required (if applicable)**

We have requested linkage to the Index of Multiple Deprivation data to test whether the outcomes of the NHS Health Checks differ across different socioeconomic status. We already have deprivation data obtained for protocol 13_071A but we will request all linked data again from the latest linkage Set (i.e. Set 12). This will ensure that we are working with the most accurate and consistent data (e.g. if a patient's postcode has been added or changed).

In addition, we are requesting ONS mortality data to enable cause of death analysis. We also plan to use integrated HES data to evaluate hospital admissions with ischaemic heart disease or stroke events. We are aware that a small number of patients may be eligible for linkage to IMD data but not eligible for linkage to the ONS mortality and inpatient HES data. This is because eligibility for linkage to IMD depends on the availability of a valid postcode, whereas eligibility for linkage to ONS and HES data depends on availability of a valid NHS number.

We will initially conduct the analysis using CPRD data only (the ‘unlinked analysis’). Subsequently, we will conduct a similar analysis using CPRD data together with linked data (the ‘linked analysis’). We will take into account the coverage period for the ONS mortality and inpatient HES data. Set 12 linkages provide ONS mortality and inpatient HES data through to 30/09/15, so the time period for the linked analysis will be restricted in comparison to the unlinked analysis. Patients who are not eligible for ONS and HES linkage will be excluded from the linked data analysis by restricting the study population to those eligible for all linkages. The loss of participants should not be large because the initial sample was drawn from linkage eligible participants.

1. **Study Population**

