The original sample was extracted from the October 2014 release of CPRD for 140,356 participants with a record of an NHS Health Check between 1 April 2010 and 31 March 2013, from 452 general practices in England. We restricted the sample to all 106,784 participants registered with 334 general practices with IMD 2010 quintile for England, linked via the participant postcode, at the lower super-output area level. We also excluded all patients who were ever treated with antihypertensive drugs (8531) or statins (1529) before the date of the check. We also excluded patients (4859) who did not have a full year of up to standard record before the date of the check and one patient whose check was after 31 March 2013. We also excluded patients with diabetes (227), coronary heart disease (2) or stroke (3) diagnosed before the check. There remained 91,618 participants who had a health check between 1 April 2010 and 31 March 2013, who had at least 12 months record, were never treated with antihypertensive drugs or statins, and were not diagnosed with diabetes, stroke or CHD before the check. For these 91,618 participants, eligible control participants were identified for 75,123 (82%) and these participants, and their matched controls, will be included in the present study.

1. **Selection of comparison group(s) or controls**

Control participants were selected if they were eligible for the NHS Health Checks but did not receive the check, they might have been invited to attend the Health Check, or not. The control participants were individually matched by general practice, gender and age with participants who received the Health Check.

1. **Exposures, Outcomes and Covariates**

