**Table 1: Case definitions for key measures:**

| **Condition** | **Read Codes** | **Therapy Codes** | **Test results** | **ICD-10 codes** |
| --- | --- | --- | --- | --- |
|  |  |  |  |  |
| **Ischaemic heart disease** | As listed in reference 9. | N/A | N/A | I20-I25 |
|  |  |  |  |  |
| **Stroke** | As listed in reference 10. | N/A | N/A | I60-I64 |
|  |  |  |  |  |
| **Diabetes mellitus** | As listed in Appendix 1. | BNF chapter 6.1.1 and 6.1.2 | HbA1c >=6.5% (48 mmol/mol) | E10-E14 |
|  |  |  |  |  |
| **Chronic kidney disease** | K05 and K06 codes | N/A | eGFR based on serum creatinine using CKD-EPI equation (11) | N18, N19 |
|  |  |  |  |  |

Secondary outcomes: CVD risk and CVD risk factors, including: smoking, BP, total cholesterol, HDL and BMI. Data on medication prescription for antihypertensive drugs, lipid-lowering drugs, antiplatelet drugs and nicotine replacement therapy will be analysed by recording drug codes to chapter subheadings in the British National Formulary (chapter 2 for CVD drugs).

1. **Data/ Statistical analysis**

The proportion of participants with values recorded for five risk factors (blood pressure, total cholesterol, HDL, BMI and smoking status) will be evaluated. Risk factor values will also be assessed. Changes over time in prescription of drugs for CVD risk management, including antihypertensive, lipid-lowering, antiplatelet and nicotine replacement therapy, will be evaluated.

The association between NHSHC and changes in CHD, stroke, diabetes and CKD clinical events will be examined using Cox hazard and Poisson regression models. Person-time approach will be adopted, where the start date is the date of the check. Hazard ratios will be estimated using Cox proportional hazards models and incident rate ratio using Poisson regression model. The proportional hazard assumptions will be tested. Linear mixed models will be used to study changes in continues outcomes (BP, cholesterol and BMI measurements). Follow-up will be censored if a control participant receives a health check at a later date. The effect of deprivation will be evaluated. Potential effect modification from deprivation category will be evaluated by testing for an interaction of health check status and deprivation category.

1. **Plan for addressing confounding**

To control for potential cofounders, model covariates will include age, gender, ethnicity and deprivation indices.

1. **Plan for addressing missing data**

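### Only controls are censored at a later health check, and that check normally requires being undiagnosed and untreated, so the censoring depends on health status and the planned models do not correct for it.

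*Protocol*

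**What the plan says.** **Censoring.** The protocol's Data/Statistical analysis section starts person-time at the date of the check and adds: "Follow-up will be censored if a control participant receives a health check at a later date". It does not state a start date for controls.

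**Who is a control.** The section on selection of comparison groups says: "Control participants were selected if they were eligible for the NHS Health Checks but did not receive the check". It gives no date by which non-receipt is judged. The Lay Summary describes "a matched control who did not initially receive a health check".

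**Who can be checked.** The Technical Summary limits the programme to adults aged 40-74 without diagnosed CVD or diabetes. The Background describes the target group as those "who have not yet developed CVD and are not treated for elevated risk".

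**Adjustment.** The confounding section names age, gender, ethnicity and deprivation. Controls are matched on practice, gender and age. The limitations section mentions neither health-dependent censoring nor selection on later data.

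**Outcomes and target.** Primary outcomes are all-cause mortality, CHD, stroke, diabetes and CKD. The power statement is for CHD: "more than 90% power to detect a risk ratio of 0.85" over three years.

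**The concern.** Cox and Poisson models treat censoring as uninformative given the covariates. Here the censoring event is a health check, and access to it depends on health. A control who is diagnosed with CVD or diabetes, or starts preventive treatment, normally stops being eligible and so stays in control follow-up. A control who remains undiagnosed and untreated can be checked and removed. The checked arm has no such removal. Over time the remaining control person-time is enriched for diagnosed and treated people. None of the four covariates captures that change.

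The effect is most direct for all-cause mortality. A control who develops CHD, stroke or diabetes remains at risk of death but is unlikely to be removed by a check. If diagnosed and treated people are at higher risk, mortality, CHD and stroke comparisons shift towards benefit.

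Diabetes goes the other way. A case detected through the check counts in the checked arm, because follow-up starts there. A control's later check ends follow-up, so a case it would reveal is lost.

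The two descriptions of controls raise a second question. A person unchecked at the start and a person who never received a check are not the same. If non-receipt was judged on records after the index date, controls were chosen partly on their future.

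**Working it through.** **1. The plan's own figure.** Inputs from the power section: "the background incidence of CHD is about 3 per 1,000 per year"; "if there are 75,000 health check participants and 182,000 control participants"; "the type 1 error rate is set at 0.05" (two-sided assumed); risk ratio 0.85; three years.

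- Control events: 182,000 × 0.009 = 1,638. Checked-arm events: 75,000 × 0.009 × 0.85 = 573.75.
- Standard error of log RR: √(1/1,638 + 1/573.75) = 0.0485. z = |ln 0.85| / 0.0485 = 3.35.
- Power = Φ(3.35 − 1.96) = 91.8%. A two-proportion test gives 92.7% and the Schoenfeld formula 93.5%.

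The stated power of over 90% reproduces. Censoring costs little of it. If controls were checked at 10% per year, mean control time would be (1 − e^(−0.3))/0.1 = 2.59 years and power 90.7%. At 20% per year it would be 2.26 years and 89.5%. The issue is bias, not power.

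**2. Bias from the censoring rule.** The true hazard ratio is set to 1. The protocol gives no rates, so these are assumptions:

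- c, the rate at which eligible controls are later checked: 5-20% per year. The five-year cycle implies at most about 20% offered per year.
- λ, the rate of new diagnosis or treatment: 3-6% per year, equal in both arms.
- k, the relative CHD risk once diagnosed or treated: 1.5-3.

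Ignoring the small event rate, the diagnosed or treated share at time t is:

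- Checked arm: a(t) = 1 − e^(−λt).
- Controls still followed: b(t) = I/(H + I), with H = e^(−(λ+c)t) and I = [λ/(λ+c)] × (1 − e^(−(λ+c)t)).
- Apparent hazard ratio: [1 + (k−1)a] / [1 + (k−1)b].

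The extreme case is λ = 0.06, c = 0.20, k = 3:

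| Year | a | b | Apparent HR |
|---|---|---|---|
| 0 | 0 | 0 | 1.00 |
| 1.5 | 0.086 | 0.099 | 0.978 |
| 3 | 0.165 | 0.214 | 0.931 |
| 6 | 0.302 | 0.465 | 0.832 |

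Averaging over three years by Simpson's rule: (1 + 4 × 0.978 + 0.931)/6 = 0.974. Over six years: (1 + 4 × 0.931 + 0.832)/6 = 0.926. Solving the Cox score equation with events included gives 0.973 and 0.923.

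Cox results for first CHD across the whole range:

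| Relative risk k | 3 years | 6 years |
|---|---|---|
| 1.5-3 | 0.97-1.00 | 0.92-1.00 |
| 1 | 1.00 | 1.00 |
| 0.7 | 1.00-1.01 | 1.00-1.02 |

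Six years is the longest possible follow-up (April 2010 to March 2016). If diagnosed or treated controls are still checked at 10% of the eligible rate, the extremes become 0.976 and 0.931. The crude Poisson rate ratio moves less, to 0.988 and 0.966.

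As a variant, suppose 20% of controls have 2-3 times the risk and 0.5-0.7 times the uptake. With uptake of 10-20% per year, the three-year rate ratio is 0.97-0.99. Mortality was not modelled separately.

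**3. If non-receipt was judged after the index date.** Index checks run from April 2010 to March 2013 and the sample came from the October 2014 release, so a window of about 1.5 to 4.5 years is possible. Suppose a control had to be unchecked for W years, and an event ends eligibility. With rare events and T = 3 years of follow-up, the null rate ratio is about e^(−cW)T / [(1 − e^(−cW))/c + e^(−cW)(T − W)].

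| Later-check rate | W = 1.5 | W = 3 |
|---|---|---|
| 5%/year | 0.98 | 0.93 |
| 10%/year | 0.96 | 0.86 |
| 20%/year | 0.92 | 0.73 |

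For example, at 10% and W = 3: 2.2225/2.5918 = 0.86. These figures apply only if selection worked this way.

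**The case against.** **Eligibility is not the same as being healthy.** A reader might infer that only healthy controls can be censored and that the remaining control time is therefore high-risk. The protocol does not support that. Undiagnosed people with high untreated risk stay eligible. The rule is also not absolute: Study Population lists 8,531 + 1,529 + 227 + 2 + 3 = 10,292 of 106,784 people with a recorded check (9.6%) who had already been treated or diagnosed. This stands, and the point is limited accordingly.

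**A much larger bias can be produced by assumption.** Suppose a fraction f of controls is censored halfway through at relative hazard h. The control rate is then inflated by (1 − 0.5fh)/(1 − 0.5f). With f = 0.4 and h = 0.5 this is 1.125, a null ratio of 0.89. That posits a low-risk class of attenders and does not model the eligibility rule. The protocol gives neither f nor h. Its only related evidence is that smokers may be under-represented among attenders.

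**For a first event, the control has already left the risk set.** True for CHD, stroke and diabetes taken singly. Bias then arises only through intermediate diagnosis or treatment, or through unmeasured risk, which is why section 2 of the working finds a small effect. The argument does not apply to mortality.

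**Selection on the future is not shown.** The Lay Summary wording and the provision for later checks indicate that non-receipt was not required throughout follow-up. How it was judged belongs to the earlier study's protocol, which is not available here. A reader might infer from the selection section that later-checked people were excluded, but the protocol does not establish it.

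**Censoring at crossover is a recognised approach, and weights or sensitivity analyses are often left to the SAP.** Both are fair. Their absence is not the fault raised here. The protocol fixes a one-sided, health-dependent censoring rule and a narrow covariate set, and leaves the control definition ambiguous.

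**Conclusion.** The concern holds in limited form. As written, censoring applies to controls only and depends on health status, and the stated adjustment does not remove that dependence. The probable direction favours the check for mortality, CHD and stroke, and runs against it for diabetes. No direction is assigned for CKD.

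The size cannot be determined from the protocol. Under the assumed uptake, transition rates and relative risks, the CHD hazard ratio shifts by about 0-3% over three years and up to about 8% over six. The shift vanishes if diagnosed or treated people have average risk and reverses if their risk is lower. Against a target of 0.85 this is not enough alone to create the effect, but it matters for a modest estimate, especially with longer follow-up.

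Selection on post-index data could produce a bias as large as the target, for example 0.86 with a three-year window and 10% annual uptake. That is a possibility to rule out, not an established defect.

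**What to change.** 1. Define a control as eligible with no check on or before the matched participant's check date, and use that date as the control's index date.
2. Confirm from the earlier study that the existing control set meets this definition, and word the Lay Summary and the selection section alike. Re-drawing controls is needed only if it does not.
3. Keep the planned censored analysis. Beside it, report one analysis that does not censor at a later check, and one with inverse-probability-of-censoring weights built from time-updated diagnoses, prescriptions, consultations and recorded risk factors including smoking.
4. Report the percentage of controls later checked.
5. List health-dependent censoring among the limitations, with its opposite expected direction for diabetes.

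The cost is extra analysis work. The uncensored contrast is somewhat diluted because some controls go on to be checked, which is why it belongs beside the planned analysis and need not replace it. Weighting depends on how well the record captures why controls were later checked.

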Since the implementation of the NHS Health Check, studies have examined the effectiveness of the programme in terms of CVD risk reduction. Cochrane, Davey (6) monitored the changes in CVD risk factors after the first year of implementing the NHSHC and assessed the benefit of the lifestyle support component of the programme. They compared participants who received the health check alone with participants who received the health check together with additional lifestyle change support. The mean CVD risk declined in both groups. In the health check group, it was 32.9% at baseline and it reduced to 29.4% (p<0.001) after one year follow up. In the health check plus lifestyle support group CVD risk was 31.9% at baseline and it reduced to 29.2% (p<0.001) after one year follow up (6). Another study aimed at assessing the CVD risk reduction after one year follow-up (7). In participants who had a completed health check (n=1886) the mean global CVD risk score was reduced significantly from 28.2% (CI= 27.3,29.1) to 26.2% (CI= 25.4, 27.1)(7). Both studies showed modest reduction in CVD risk and CVD risk factors. However, participants were only followed after one year. Since the NHSHC was introduced in 2009, long term follow up would provide further assessment of the programme’s effectiveness, which this study aims to achieve.

The present analysis will draw upon our previous CPRD study on health checks (Protocol: 13_071A). (8) The previous study constructed a matched cohort design in which participants who had received health checks between 1 April 2010 and 31 March 2013 and who had at least 12 months records, were compared with controls who did not receive a health check. This previous study focused on risk factor detection and showed that health checks are associated with increased detection of hypercholesterolaemia, and to a lesser extent obesity and hypertension, but smokers may be under-represented among participants in the programme. The proposed study aims to evaluate longer term follow-up of substantive health outcomes. This study aims, therefore, to evaluate changes in risk factors, clinical events and mortality outcomes. In this proposed study, all individuals will have the potential to provide a minimum of three years of follow-up following the health check.

1. **Study Type**

The study will be hypothesis testing, estimating health check programme through a comparison of health check and control participants.

1. **Study Design**

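### The confounding plan does not name baseline smoking, although the protocol warns that smokers may be under-represented among attenders, so self-selection could look like a health-check benefit

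*Protocol*

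**What the plan says.** The Protocol's section Plan for addressing confounding is one sentence, and its content is that "model covariates will include age, gender, ethnicity and deprivation indices". Under Selection of comparison group(s) or controls, controls were "individually matched by general practice, gender and age with participants who received the Health Check". The same section describes them as eligible people who "did not receive the check, they might have been invited to attend the Health Check, or not", so they can include people who were invited and stayed away.

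The Background summarises the sponsor's previous CPRD study and says that "smokers may be under-represented among participants in the programme". The Sample Size section confirms that the present study intends to use the same 75,123 attenders and 182,245 controls.

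Smoking does appear under Exposures, Outcomes and Covariates, but as a secondary outcome: "CVD risk and CVD risk factors, including: smoking, BP, total cholesterol, HDL and BMI". No section names smoking before the check as an adjustment variable. The Limitations section concedes that the design is not randomised and that smoking and BMI may be misclassified. It does not mention self-selection.

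**The concern.** Objective 2 hypothesises fewer deaths and clinical events in attenders. People who accept a preventive check may differ from those who do not, and the protocol itself points to smoking as one such difference. Smoking raises the risk of death, CHD and stroke. Fewer smokers among attenders would therefore move these hazard ratios in the same direction as the hypothesised benefit. The model as described could not tell the two apart.

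Sample size does not help. A larger cohort narrows the confidence interval around a biased estimate, and this cohort is large enough for a modest bias to reach nominal significance. The protocol treats smoking status as a variable recorded in CPRD, so a baseline value can be sought in data the study already uses.

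**Working it through.** **Step 1: what the covariates add.** Matching covers practice, gender and age. The model covers age, gender, ethnicity and deprivation. Only ethnicity and deprivation are new.

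**Step 2: reproduce the plan's power figure.** The inputs come from Sample power calculation: "background incidence of CHD is about 3 per 1,000 per year", "the type 1 error rate is set at 0.05" (taken here as two-sided, since the protocol does not say), 75,000 attenders, 182,000 controls, three years and a risk ratio of 0.85.

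- Control events: 182,000 × 3 × 0.003 = 1,638.
- Attender events at 0.85: 75,000 × 3 × 0.003 × 0.85 = 573.75.
- SE of the log rate ratio: √(1/573.75 + 1/1,638) = 0.0485.
- z = |ln 0.85| / 0.0485 = 0.1625 / 0.0485 = 3.35.
- Power = Φ(3.35 − 1.96) = 0.918.

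A two-proportion calculation gives 92.7% and the Schoenfeld formula 93.5%. The stated power of more than 90% is reproduced.

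**Step 3: the smallest effect that reaches significance.** With no true effect, expected CHD events are 75,000 × 3 × 0.003 = 675 and 1,638. The SE is √(1/675 + 1/1,638) = 0.0457. An observed ratio below exp(−1.96 × 0.0457) = 0.914 is nominally significant.

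**Step 4: bias from smoking alone.** Let p_a and p_c be the smoking prevalences in attenders and controls, and R the smoking risk ratio. With a true health-check ratio of 1,

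apparent HR = [1 + p_a(R − 1)] / [1 + p_c(R − 1)].

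The two-sided false-positive rate is Φ(−m − 1.96) + Φ(m − 1.96), where m = ln(apparent HR) / 0.0457. All values of p_a, p_c and R below are assumptions, because the documents give none.

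| Smokers, attenders v controls | R | Apparent HR | False-positive rate (nominal 5%) |
|---|---|---|---|
| 15% v 18% | 1.5 | 1.075/1.09 = 0.986 | about 6% |
| 15% v 20% | 2 | 1.15/1.20 = 0.958 | about 15% |
| 15% v 20% | 3 | 1.30/1.40 = 0.929 | about 37% |
| 12% v 22% | 3 | 1.24/1.44 = 0.861 | about 90% |

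Recomputing the SE with the slightly lower attender event count changes the last three rates to about 15%, 35% and 87%. The false-positive rates apply to CHD only, because the protocol states a background rate for no other outcome. The apparent HR formula applies equally to mortality and stroke, with the R for that outcome.

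**Step 5: what the formula leaves out.** It uses the crude difference in smoking. Any part of that difference explained by practice, deprivation or ethnicity is already handled by the design or the model. Only the remainder biases the estimate, and the documents do not allow it to be estimated.

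**The case against.** The evidence is hedged. The Background says smokers may be under-represented, gives no prevalence, and does not say whether the comparison was with these matched controls or with a wider population. A reader might infer that the protocol reports an established imbalance of known size. It does not, and at the mild end of the range the effect is negligible.

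The covariate sentence lists what the models will include and does not exclude anything else. A fuller list could appear in an analysis plan that is not shown. A reader might infer that all other covariates are ruled out, and the wording does not go that far. Still, this is the section meant to deal with confounding, and it names no risk factor at all, including the one the protocol flags.

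A reader might also infer that BMI, blood pressure, cholesterol and consultation rate are known to be imbalanced in the attenders' favour. The documents show no such thing. The Background reports greater detection of hypercholesterolaemia, obesity and hypertension with checks, which is a different matter from baseline imbalance. Study Population also excludes attenders with earlier antihypertensive or statin treatment, diabetes, CHD or stroke, and controls had to be eligible for a check. These restrictions limit some baseline differences, but they do not balance smoking.

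Finally, the protocol openly calls the assessment non-randomised. That is a fair caveat, but it does not stand in for adjusting on a recorded confounder.

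**Conclusion.** The point holds for smoking and for the Objective 2 models. The protocol flags a possible selection difference in this very cohort, the difference would act in the direction of the hypothesis, and the stated adjustment set does not address it. Under the assumptions shown, smoking alone could produce a null hazard ratio anywhere from 0.99 to 0.86, against the 0.85 used in the power calculation. The documents cannot place the true bias within that range, and matching and deprivation adjustment may shrink it.

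This should be fixed before analysis. The documents do not support calling it a fatal flaw, because the evidence of imbalance is tentative and the size rests on assumed prevalences and risk ratios. They also do not support a general claim of imbalance in the other risk factors.

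**What to change.** In Plan for addressing confounding, add wording to this effect:

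*For the Objective 2 Cox and Poisson models, covariates will also include smoking status recorded before the index date, using the same look-back in both groups. Values first recorded at the check will not be used. Missing values will be handled by multiple imputation, assuming data are missing at random given the variables in the imputation model.*

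The restriction to earlier records matters because the protocol treats recording of risk factors as an outcome of the programme, so values taken at the check would differ in availability between groups. Study Population gives attenders at least a year of prior record; the same requirement should be stated for controls.

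Add pre-index BMI, systolic blood pressure and cholesterol as a sensitivity analysis for the same models only. They should not become blanket covariates in the linear mixed models, where blood pressure, cholesterol and BMI are the outcomes and adjustment would change what is estimated. Name self-selection in the Limitations section. A negative-control outcome from the ONS cause-of-death data already requested is optional, if event numbers allow.

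The cost is protocol wording and modest extra analysis of data already held or requested. The main drawback is that pre-index values are likely to be incomplete in both groups, and the missing-at-random assumption may be questioned because testing depends on who consults. That assumption should be stated openly.
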